#### 11.4.2 Primary Analysis

A Cox proportional hazards regression model with time to the (combined) primary endpoint as the response and treatment arm as the explanatory variable will be fitted, stratified after study centre, prednisone dose, and age group. Non-inferiority will be concluded if the two-sided 95% confidence interval of the hazard ratio (HR) between the experimental and the control arm lies entirely below the critical HR ratio of 1.478. The analysis will be conducted on the PP set.

#### 11.4.3 Secondary Analyses

Secondary outcomes:

**Performance of the 250 mcg corticotropin stimulation test.** If this test is clinically relevant, it is assumed that in patients with a normal test result, the two study arms will not differ with regard to the primary outcome, whereas patients with a pathological test result will experience an event more often after the rapid termination (experimental arm) than after tapering (control arm). It is thus hypothesized that there is an interaction between the test result and the glucocorticoid withdrawal scheme. To test for a significant interaction, the Cox proportional hazard regression model used to assess the primary objective is extended by the stimulation test result (passed vs. failed) and its interaction with the treatment group (rapid vs. tapering). If a significant interaction is found, subgroup analyses are performed for the two treatment groups in order to estimate the strength of the association between test result and primary outcome.

---

**The time to first occurrence of individual components** of the primary outcome is, in analogy to the (composite) primary outcome, also analysed with Cox proportional hazards regression models.

Cumulative overall systemic glucocorticoid dose, cumulative systemic glucocorticoid dose administered to treat or prevent adrenal failure, cumulative systemic glucocorticoid dose administered to treat relapse of disease (specified for each disease), general health status as self-assessed by the patients on a VAS, blood pressure (supine and standing), hospital length of stay, weakness, hypothermia, nausea, vomiting, abdominal pain, and fatigue are analysed with linear regression models.

In all analyses, the variables for which randomisation was stratified (center and age group) are included as covariates for adjustment. If model assumptions are not met, transformations of outcome variables and the use of generalised linear (instead of linear) models are considered.

Besides the secondary outcomes, potential glucocorticoid-induced side effects will be assessed and documented on the CRF. Proportions of side effects will be compared between treatment groups and analyzed using logistic regression.

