### **4.3 Secondary Objectives**

The secondary objectives of this trial are:

- To establish the clinical relevance of the 250 mcg ACTH (Synacthen®) stimulation test.
- To establish the relationship between clinical signs and symptoms of hypocortisolism and biochemical adrenocortical performance

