### 5.4 Safety Outcomes

The individual components of the primary outcome are defined as safety outcomes. The occurrence of an adrenal crisis is of particular relevance due to its obvious danger for the patient. At the same time, papers reporting unequivocal, non-circumstantial evidence of true glucocorticoid-responsive shock in **secondary** (glucocorticoid-induced) adrenal insufficiency are exceedingly rare and date back well into the last century. Because it is not realistic to choose this event as single endpoint, it was defined as one component of the composite primary outcome.

Judging from the literature, it is likely that the imminent danger of adrenal crisis in secondary adrenal insufficiency is overestimated quantitatively. This is supported by our own data from the REDUCE trial. As in the REDUCE trial, patients in this trial will receive a written instruction on signs and symptoms of hypocortisolism and will be provided with five 10 mg tablets of prednisone to cover increased needs for glucocorticoids in emergency situations. This approach has proven effective in the REDUCE trial, where approximately one third of the study patients were discharged from the hospital with biochemically suppressed adrenal glands, but not a single critical incident was provoked by glucocorticoid deficiency during 6 months of follow-up.

---

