#### Assessment tools of 2° outcome measures:

- Questionnaire: individual components of 1° outcome; SF-12 survey; symptoms of hypocortisolism
- Signs of hypocortisolism, in subgroup as specified in above table: measure blood pressure (supine and standing), measure heart rate.
- Treating physician interview: cumulative systemic overall glucocorticoid dose? Cumulative systemic glucocorticoid dose to treat or prevent adrenal failure? Cumulative systemic glucocorticoid dose to treat relapse of underlying disease?
- Perform 250 mcg ACTH (Synacthen®) test\*: in subgroup as specified in the above table.
- Measure HbA1c value: in subgroup as specified in the above table.
- Determine length of hospital stay (if hospitalized upon study inclusion): Study hospital chart

\*The 250 mcg ACTH (Synacthen®) test is a routine procedure for the assessment of the functional status of the hypothalamus-pituitary-adrenal axis. The test is performed as follows. It can be done at any time during the day without the need of a fasting state. A blood sample is drawn for measurement of baseline serum cortisol. 1 ampoule (250 mcg) of tetracosactide (beta-1-24 – corticotropin; Synacthen®) is injected intravenously. 30 and 60 minutes after the injection, blood samples are drawn for measurement of stimulated serum cortisol.

The 2° outcomes will be assessed by telephone on days 7, 28, 35, 90, and 180. Additionally, a subgroup of 180 patients will be seen for a clinical visit on study days 7 and 35. These clinical visits include vital signs (heart rate, blood pressure while in recumbent and upright position, and a 250 mcg Synacthen® test.

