#### 9.2.4.2 Laboratory parameters

In menstruating females willing to participate in the trial, a urine pregnancy test will be performed at the screening

---

visit.

In all trial participants, a 250 mcg Synacthen® test will be performed on study day 1. Results will be concealed until the end of the trial.

In all trial participants, the serum remaining from the basal cortisol measurement will be frozen at -20°C as reserve for later batch analyses.

In a subgroup of 180 patients the 250 mcg synacthen test as well as the storage of 5 ml reserve serum will be repeated on study days 7 and 35.

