- The non-inferiority margin is defined as an absolute increase of the event rate by 13% over 6 months. We used a modified Delphi approach to determine this margin. 10 experienced clinicians board-certified in internal medicine and/or rheumatology, gastroenterology, and endocrinology were individually asked to define the maximum increase in outcome events they would accept for the benefit of rapid glucocorticoid stop and gain of high-quality scientific data in the area of steroid withdrawal. Assuming an event rate of 40% in the standard treatment arm, the mean tolerable increase under experimental treatment was 13.6% (range, 5 to 20%; median, 13%).
- The significance level is 5%.

For each combination of the noninferiority margins 7.5%, 7.6%, ..., 17.5%, and the sample sizes  $n = 200, 210, \dots, 1200, 999$  individual data sets were simulated based on the above assumptions. A Cox proportional hazards regression model was fitted to each data set, and the hazard ratios for the experimental vs. the control arm with the associated 95% confidence interval were estimated. Noninferiority was concluded if the upper limit of the two-sided 95% confidence interval of the hazard ratio was below the critical hazard ratio (see above equation). The power was estimated as the proportion of positive conclusions divided by the total number of the 999 iterations per parameter combination. To achieve a power of 80%, 573 patients (95% CI, 565 to 580) need to be included, assuming an event rate of 40% over the 6 months follow-up period and setting the non-inferiority margin to 13% (Figure). The critical hazard ratio for this noninferiority scenario is 1.478.

The sample size of  $n=573$  is a conservative estimation, since the assumed drop-out rate of 10% is relatively high.

[figure not shown]

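### The ACTH-test interaction rests on a passed/failed term alone; a pre-specified continuous-cortisol model should stand beside it

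*Protocol*

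**What the plan says.** Section 4.3 lists as its first secondary objective: "To establish the clinical relevance of the 250 mcg ACTH (Synacthen®) stimulation test". Section 11.4.3 turns this into an interaction hypothesis by test class. For one class it expects this: "in patients with a normal test result, the two study arms will not differ with regard to the primary outcome". For the other class, those who fail, it expects events to be commoner under the abrupt stop than under the taper. The test of this hypothesis is the primary Cox model "extended by the stimulation test result (passed vs. failed) and its interaction with the treatment group (rapid vs. tapering").

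The underlying measurement is not binary. On sampling, section 9.2.2 says that after a baseline draw "30 and 60 minutes after the injection, blood samples are drawn for measurement of stimulated serum cortisol". On coverage, section 9.2.4.2 says: "In all trial participants, a 250 mcg Synacthen® test will be performed on study day 1". The German-language summary gives different sampling times for Germany, namely 0 and 60 minutes.

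The list of subgroup analyses in section 11.4.3 also names the test result (item 6), without fixing its form. Section 11.4 leaves detailed methodology to a statistical analysis plan, and section 11.4.6 requires a protocol amendment for substantial deviations from the analyses outlined.

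**The concern.** A passed/failed term treats a patient with almost no cortisol response like one just under the line, and treats patients just either side of the line as different. If the risk after an abrupt stop rises gradually as the response falls, this discards information in an interaction test that was not the basis of the sample size.

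The second issue is interpretation. Section 3.1 calls the relevance of the test unclear. It cites a surgical study in which the stimulated level correlated with the level during the operation, yet none of 31 patients with a blunted response had manifest insufficiency. Where the cut should lie is therefore part of the open question. With pass/fail alone, a null interaction could mean that the test is uninformative or that the line is in the wrong place, and the analysis cannot tell these apart. Section 3.7 names as a benefit of the trial its evidence on whether the test can stratify patients by their need for tapering, so the distinction matters.

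**Working it through.** **1. The plan's own figure.** On sample size, section 11.2 says: "To achieve a power of 80%, 573 patients (95% CI, 565 to 580) need to be included". Its inputs are 40% events in each arm, a 13-point margin, 10% drop-out and a two-sided 95% interval.
- Critical HR = ln(0.60 − 0.13)/ln(0.60) = 1.478, as stated.
- Events = 4 × (1.960 + 0.842)² / (ln 1.478)² = 206.
- Patients = 206/0.40 = 515, and 515/0.90 = 572.2, so 573. This matches.

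The protocol gives no failing share, effect size or power for the interaction, so these must be assumed. The only anchor for the failing share is in section 5.4, on the earlier trial: "approximately one third of the study patients were discharged from the hospital with biochemically suppressed adrenal glands". I used one third, with a range of 20% to 60%.

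**2. Analytic check for a log-linear effect.** With drop-out spread uniformly, the event probability is 0.382, giving 573 × 0.382 = 219 events. For 80% power with a continuous, normally distributed marker, the interaction log HR per SD is 2.802/√(219/4) = 0.379, an HR of 1.46. Cutting that marker at failing share q keeps a fraction RE = φ(z_q)²/[q(1 − q)] of the information. Power then becomes Φ(2.802 × √RE − 1.960).

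| Failing share | RE | Pass/fail power (continuous 80%) | Loss, points |
|---|---|---|---|
| 20% | 0.490 | 50% | 30 |
| one third | 0.595 | 58% | 22 |
| 50% | 0.637 | 61% | 19 |
| 60% | 0.622 | 60% | 20 |

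At 50% continuous power the losses are 15 to 22 points.

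**3. Simulated Cox models.** Settings: N = 573, 1:1 allocation, 40% events over 6 months, 10% uniform drop-out, two-sided 5% test, 1,000 to 1,500 runs per scenario (Monte Carlo error about 1 to 1.3 points at 1,500 runs). Effects are log HRs for the arm interaction: per SD fall in cortisol for log-linear; per SD below the cut for ramp; the full contrast for S-shape and step.

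| Failing share | Shape of effect | Continuous (linear) | Pass/fail | Pass/fail minus continuous |
|---|---|---|---|---|
| one third | log-linear, 0.30 | 60% | 39% | −21 |
| one third | log-linear, 0.38 | 81% | 61% | −19 |
| one third | log-linear, 0.40 | 83% | 63% | −20 |
| one third | ramp below cut, 0.7 | 50% | 40% | −10 |
| one third | ramp below cut, 1.0 | 84% | 69% | −15 |
| one third | S-shape at cut, 0.95 | 72% | 72% | 0 |
| one third | step at cut, 0.693 | 53% | 72% | +19 |
| one third | step at cut, 0.75 | 62% | 83% | +20 |
| one third | step at cut, 0.95 | 82% | 96% | +14 |
| 20% | log-linear, 0.38 | 79% | 53% | −25 |
| 20% | ramp, 1.5 | 74% | 73% | −2 |
| 20% | step, 0.75 | 44% | 68% | +24 |
| 50% | log-linear, 0.38 | 79% | 58% | −22 |
| 50% | ramp, 0.65 | 78% | 53% | −25 |
| 50% | step, 0.75 | 65% | 85% | +20 |
| 60% | log-linear, 0.38 | 79% | 57% | −21 |

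Differences are taken before rounding.

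**4. Linear term or spline.** With one third failing, a piecewise-linear term (2 df, knot at the cut) had 85% power against 76% for the linear term under a ramp of 0.9, but 66% against 76% under a log-linear effect of 0.36. Under a step of 0.693 it had 42%, against 53% linear and 72% pass/fail. No single form is best throughout.

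**The case against.** The strongest counter-argument is that pass/fail fits the question asked. The hypothesis is worded by class, and the practice under study is a decision rule: a low result leads to tapering. A log-linear effect over the whole range would let the arm effect vary among patients with normal tests, where section 11.4.3 assumes none. Under the simplest reading, a step at the cut, a linear term has clearly less power. This stands, and it is why pass/fail should remain the formal test. It does not settle the matter: an effect that is null above the cut and graded below it also fits the stated hypothesis, and there pass/fail loses 10 to 15 points with one third failing.

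It can also be said that functional form and supportive models belong in the analysis plan, which is not at hand. That is fair for the cut value and the sampling time, and their absence from the protocol is no defect. The scale of the test result, however, is something section 11.4.3 does state, in one form only.

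A reader might infer more than the documents support:
- **That dichotomising is an error and pass/fail should be replaced or demoted.** The step results argue against this.
- **That the loss is a fixed 15 to 20 points whenever the effect is graded.** It is near zero for an S-shaped effect around the cut.
- **That this is the main secondary analysis.** The synopsis gives that label to the individual components and the cumulative doses.
- **That a peak of the 30- and 60-minute values is available everywhere.** The German-language summary indicates otherwise for Germany.

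**Conclusion.** The point holds as an inexpensive improvement to a secondary analysis. It does not touch the primary outcome, the sample size or the non-inferiority conclusion.

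Relying on pass/fail alone costs roughly 10 to 20 points of interaction power with about one third failing, if the effect is log-linear or graded below the cut. Over other graded shapes and failing shares the loss is about 0 to 30 points. Under an exact step, pass/fail is better by about 14 to 20 points with one third to one half failing, and by 24 in the one scenario with 20% failing.

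These figures assume a normally distributed marker on a suitable scale, no prognostic effect of cortisol in the control arm, an unstratified Cox model, and a failing share that the protocol does not give for this trial. Because the ranking of the two models turns on an unknown shape, the weakness is reliance on one of them alone. The gain in interpretation, separating an uninformative test from a misplaced cut, does not depend on any of the power figures.

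**What to change.** In section 11.4.3:
- Keep the passed/failed interaction as the formal test of the class-based hypothesis, and say so in advance.
- Add a model, fixed before unblinding, in which stimulated cortisol enters the primary Cox model as a continuous term with its interaction with arm. Choose a linear term or a low-order spline beforehand.
- Report the abrupt-versus-taper hazard ratio with its 95% confidence interval across the cortisol range, whether or not the formal test is significant.
- Use the 60-minute value, which both descriptions of the sampling contain. Reconcile section 9.2.2 with the German-language summary on sampling times in Germany.
- Use the same continuous form for subgroup item 6.

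The cost is a few sentences and one extra model on data already being collected. The test results stay concealed until the end of the trial (section 9.2.4.2), so there is time to fix the form. The downside is a second interaction result that may disagree with the first, which is why the formal test must be named beforehand.

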### 11.2 Determination of Sample Size

To assess the primary outcome measure, a Cox proportional hazards regression model will be fitted to the data. Non-inferiority will be concluded if the two-sided 95% confidence interval of the hazard ratio between the experimental and the control arm lies entirely below the critical hazard ratio defined as

$$HR = \frac{\lambda_e}{\lambda_c} = \frac{\frac{-\log(\pi_{et})}{t}}{\frac{-\log(\pi_{ct})}{t}} = \frac{\log(\pi_{et})}{\log(\pi_{ct})} = \frac{\log(\pi_{ct} - m)}{\log(\pi_{ct})}$$

where  $\lambda_e$  and  $\lambda_c$  are the hazard rates in the experimental and control arms,  $t$  is a fixed point of time,  $\pi_{et}$  and  $\pi_{ct}$  are the proportions of event-free patients at time  $t$ , and  $m$  is the non-inferiority margin expressed as the additional proportion of patients having had an event in the experimental arm, assuming that the occurrence of events follows an exponential distribution. Noninferiority will be concluded if the upper limit of the two-sided 95% confidence interval of the hazard ratio lies below the critical hazard ratio.

For the sample size estimation, the following assumptions were made:

- Patients are randomized to the control and experimental arms in a 1:1 ratio.
- After inclusion, all patients are followed for 6 months. Patients without an event within 6 months are considered right-censored and are not followed any further even though the trial might be ongoing.
- 10% of patients drop out within the 6 months follow-up period. The drop-out events are distributed uniformly over this period.
- The event rate within the 6 months follow-up period, i.e., the proportion of patients with an event, is 40%, both for the control and the experimental arms. We estimated this overall figure based on expected relapse rates for the various eligible diseases, as indicated by clinical experts and published data, e.g. in COPD or inflammatory bowel disease. Our estimation is conservative since the other components of the combined primary outcome will contribute to the event rate.
- The survival curves in the control and experimental arms follow the same exponential distribution. The rate parameter of the exponential distribution is chosen so that the corresponding cumulative distribution function value at 6 months equals the assumed event rate.

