#### **11.4.5 Safety analysis**

Two types of safety analyses will be performed: periodic analyses for the DSMB's meetings, and a final safety analysis at the end of the trial.

Safety analyses for DSMB meetings will summarize the rates of safety outcomes (as defined above, section 10) pooled over both treatment arms. Event types and relevance as defined for SAEs will be included in the report. The DSMB has the right to request an analysis stratified by treatment arm, or completely unblinded in case of concern for patient safety. Safety analysis for the DSMB is performed by the independent DSMB statistician.

The final safety analysis for the trial will summarize the rates of safety outcomes stratified by treatment arm and will be performed by the trial statistician after study completion.

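### Cox regression fixed for adrenal crisis will often give no usable hazard ratio or bound at the event counts the protocol points to

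*Protocol*

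**What the plan says.** Section 4.2 makes the feasibility and safety of rapid termination the primary objective. Section 5.4 defines the components of the primary outcome as the safety outcomes. On one of them it says: "The occurrence of an adrenal crisis is of particular relevance due to its obvious danger for the patient". It recalls that in the sponsor's earlier trial "not a single critical incident was provoked by glucocorticoid deficiency during 6 months of follow-up", and concedes that crisis could not realistically stand alone as an endpoint.

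The protocol names two analyses for this component:

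- **Section 11.4.3.** Time to each component "of the primary outcome is, in analogy to the (composite) primary outcome, also analysed with Cox proportional hazards regression models". The section adds centre and age group as covariates in all analyses.
- **Section 11.4.5.** "The final safety analysis for the trial will summarize the rates of safety outcomes stratified by treatment arm". No interval is mentioned.

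The composite itself is sized in 11.2. Noninferiority is concluded "if the upper limit of the two-sided 95% confidence interval of the hazard ratio lies below the critical hazard ratio", and the assumed six-month event rate "is 40%, both for the control and the experimental arms".

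**The concern.** A method that suits an outcome with a 40% event rate is carried over by analogy to an outcome for which the protocol's own evidence suggests almost no events. A Cox hazard ratio needs events in both arms to be finite. If either arm has none, the model supplies no usable estimate and no upper limit, and the rates by arm do not supply one either. What is at stake is the ability to say how large a crisis risk, or an excess risk, the trial has excluded. The composite does not answer that question, because its event rate is based on expected disease relapse.

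**Working it through.** **1. The plan's own figure (composite).**
- Critical HR = ln(0.60 − 0.13)/ln(0.60) = 1.478, as stated.
- Schoenfeld events for 80% power, two-sided 5%, 1:1: 4 × (1.96 + 0.842)² / (ln 1.478)² = 205.7, so 206.
- 206/0.40 = 515, and 515/0.90 = 572.2, so 573. This agrees with 11.2: "To achieve a power of 80%, 573 patients (95% CI, 565 to 580) need to be included".
- At 1:1, 573 patients are 287 and 286 per arm, so the composite expects events in the hundreds. The protocol gives no corresponding figure for adrenal crisis.

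**2. How often would an arm have no crisis?** The protocol states no crisis rate, so the risks below are assumptions, taken as equal in both arms. The chance of none in one arm is q = (1 − p)^287. The chance that at least one arm has none is 1 − (1 − q)².

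| Assumed risk p | Expected crises per arm | q | At least one arm empty |
|---|---|---|---|
| 0.1% | 0.3 | 75% | 94% |
| 0.5% | 1.4 | 24% | 42% |
| 1% | 2.9 | 6% | 11% |

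**3. What the Cox model returns.**
- *0 v 0:* there is no event term in the partial likelihood, hence no estimate and no interval.
- *k v 0:* the likelihood rises without limit in the log HR. In a fit with 6 v 0 and 10% drop-out, iteration stopped at a log HR of 20.2 with a standard error of 9,953. The Wald limits are 20.2 ± 1.96 × 9,953, roughly ±19,500 on the log scale, which is no information.
- *6 v 1:* the fit is finite but wide, with HR 6.0 (95% CI 0.72 to 49.9).

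**4. What the same model can still detect.** For k v 0, ignoring the small change in risk sets over time:
- Likelihood-ratio chi-square = 2k ln(573/287) = 1.383k. For k = 4 this is 5.53 (p = 0.019); for k = 6 it is 8.30 (p = 0.004).
- Log-rank (score) chi-square ≈ 0.9965k. For k = 4 this is 3.99 (p = 0.046); for k = 6 it is 5.98 (p = 0.014).

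Detection of a one-sided cluster is therefore possible. What is missing is an estimate and a bound.

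**5. What exact or score intervals give.**
- With no crisis, the exact two-sided 95% upper limit per arm is 1 − 0.025^(1/n): 1.28% for n = 287, and 1.42% for n = 258 (10% loss).
- With 0 v 0, the score upper limit of the risk difference is about z²/(n + z²): 3.84/(287 + 3.84) = 1.32%, or 1.47% for n = 258.
- With 6 of 287, the exact 95% interval for that arm is 0.77% to 4.49%.

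**The case against.** The strongest reply is that much of this belongs in the statistical analysis plan. Section 11.4 defers detailed methodology to it, and exact intervals or penalised fits for a sparse secondary outcome are typical content there. Naming Cox for time-to-event components is conventional and does not forbid further summaries. This limits the weight of the point but does not remove it: the protocol does not leave the method open. It names one, and that method often fails at the counts section 5.4 suggests. The fallback in 11.4.3 for unmet assumptions (transformations, generalised linear models) does not address a divergent Cox fit.

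Four stronger readings are tempting, and the document does not support them.

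- *A cluster of crises after abrupt stopping would go unnoticed.* The protocol names no Wald test, likelihood-ratio and log-rank tests flag 4 v 0, and 11.4.5 would show the counts by arm. The DSMB may also ask for results by arm.
- *A non-significant component will be reported as proof of safety.* No section says so. It can only be inferred from the safety objective.
- *Crisis is ranked above every other harm, or is declared to be exceedingly rare.* Section 5.4 gives it particular weight, not first rank, and its remark on rarity concerns published reports of unequivocal shock. The trial's definition in 5.1 also includes glucocorticoid-responsive hypotension.
- *A noninferiority margin for crisis is missing.* None is required for one secondary component. Limited power for a rare event follows from the sample size, and the composite's tolerance of some excess follows from the accepted 13-point margin. Neither is an error in the component analysis.

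**Conclusion.** The point holds in a limited form. For adrenal crisis, the one inferential method the protocol fixes would often yield no finite hazard ratio and no usable interval, and the descriptive rates carry no interval. As written, the plan gives no bound on a risk that bears on its primary objective. How often this happens depends on assumed crisis risks: about 94%, 42% and 11% of trials at 0.1%, 0.5% and 1% in both arms. The failure of the interval refers to the usual Wald form, which is an assumption because the protocol does not name one. The primary noninferiority conclusion is unaffected. This is an inexpensive improvement to the safety analysis, not a fault in the trial's main test.

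**What to change.** In 11.4.3 and 11.4.5, for adrenal crisis (and for death if deaths are sparse):

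- Make the main analysis the number and proportion per arm with exact (Clopper–Pearson) 95% intervals, and the risk difference with an exact or score 95% interval.
- If a hazard ratio is also reported, use Firth-penalised Cox regression with a profile-likelihood interval, without the centre and age-group covariates, which a handful of events cannot support.
- State that any safety statement on adrenal crisis quotes the upper 95% limit of the excess risk.

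The cost is a few sentences and a standard calculation, with no new data and no change in sample size. The drawback is that the statement becomes a bound: at best about 1.3% per arm, or 1.4% after 10% loss.

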### 5.2 Secondary Outcomes

1. Time to first occurrence of individual components of the primary outcome;
2. Cumulative overall systemic glucocorticoid dose;
3. Cumulative systemic glucocorticoid dose administered to treat or prevent adrenal failure;
4. Cumulative systemic glucocorticoid dose administered to treat relapse of disease, specified for each disease;
5. General health status as self-assessed by the participant on a visual analog scale (VAS) from 0 to 100, assessed at days 1, 7, 28, 35, 90, 180;
6. Score of symptoms and signs of hypocortisolism: weakness, hypothermia, nausea, vomiting, abdominal pain, fatigue, dizziness (assessed in structured interviews at time points: days 1, 7, 28, 35, 90, 180). Blood pressure (supine and standing) is assessed day 1 in all participants, but due to limited resources only in a subgroup of 180 patients living near their respective study center on days 7 and 35.
7. Performance in 250 mcg ACTH (Synacthen®) test: test assessed day 1 in all participants, plus days 7 and 35 in a subgroup of 180 patients,
8. In patients hospitalized at study entry: length of hospital stay.

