## 6.2 Methods of minimising bias

### 6.2.1 Randomization

The CTU Basel will generate the randomization list, which will be concealed to all study personnel. Patients will be randomly assigned in a 1:1 ratio, stratified according to trial site, age group, and daily prednisone dose at inclusion, to either prednisone in decreasing doses over 4 weeks or placebo. The randomisation procedure will be implemented into the electronic data capture software SecuTrial®. It will include a standard minimisation algorithm which will ensure that the treatment groups are balanced within each stratum. To avoid predictable alternation of treatment allocation, and thus potential loss of allocation concealment, patients will be allocated with a probability of 70 percent to the treatment group that would minimise the difference between the groups within the patient's stratum. Study medication will be pre-packed in glass vials; vial numbers will correspond to the pertinent number on the randomization list.

---

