### **9.3.2 Day 1 (visit 2)**

Measure heart rate and blood pressure in recumbent and supine position after at least 5 minutes resting. Randomize patient. Perform 250 mcg Synacthen® test. Draw blood for reserve serum. For reserve serum: centrifuge sample, pipet serum into 1 ml aliquots, store at -20°C. Assess VAS for general health status. Fill out CRF. Dispense trial medication. Schedule visit 3.

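### Section 11.4.3 omits daily prednisone dose when it lists the stratification variables for the secondary models, and it gives no analysis of the declared seven-item symptom score

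*Protocol*

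**What the plan says.** **Stratification factors.** Section 6.2.1 describes a minimisation algorithm with allocation "stratified according to trial site, age group, and daily prednisone dose at inclusion". Section 11.4.2 fits the primary Cox model "stratified after study centre, prednisone dose, and age group". Section 11.4.3, in a sentence covering every secondary analysis, says that "the variables for which randomisation was stratified (center and age group) are included as covariates for adjustment".

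**Symptoms.** Section 5.2 declares outcome 6 as "Score of symptoms and signs of hypocortisolism: weakness, hypothermia, nausea, vomiting, abdominal pain, fatigue, dizziness". Section 11.4.3 ends its list of continuous outcomes with "weakness, hypothermia, nausea, vomiting, abdominal pain, and fatigue are analysed with linear regression models". It names neither a score nor dizziness.

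**Day-1 values.** General health is recorded on a "visual analog scale (VAS) from 0 to 100, assessed at days 1, 7, 28, 35, 90, 180". Section 5.2 puts the symptom interviews on the same days. It also has blood pressure, supine and standing, taken on day 1 in everyone, and on days 7 and 35 only in the subgroup of 180. Section 11.4.3 names no day-1 value as a covariate.

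**Posture.** The day-1 instruction in 9.3.2 reads "Measure heart rate and blood pressure in recumbent and supine position after at least 5 minutes resting". Sections 9.3.3 and 9.3.5 repeat this pair of positions for the clinical visits, and 9.2.4.3 has an equivalent pair.

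**The concern.** The covariate sentence in 11.4.3 claims to repeat the randomisation factors but lists two of the three. An analyst who follows the list drops dose. Minimisation makes the arms more alike on dose than chance would. A model that ignores dose does not credit this, so its standard errors are too large to the extent that dose is prognostic.

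The symptom wording has a different consequence. A declared secondary outcome has no stated analysis, six single-item analyses stand in its place, and one collected item disappears. The score bears on the secondary objective in 4.3 of relating the symptoms and signs of hypocortisolism to adrenocortical performance.

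The posture wording matters because a standing pressure that a site never takes cannot be recovered at analysis.

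**Working it through.** **1. The sample size is not involved.** The critical hazard ratio is ln(0.60 − 0.13)/ln(0.60) = 1.478, as stated in 11.2. Schoenfeld's formula gives 4 × (1.960 + 0.842)² / (ln 1.478)² = 206 events. Then 206/0.40 = 515, and 515/0.90 rounds up to 573, which is the stated figure. Nothing below changes it.

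**2. The passages side by side.**

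| Item | Stated in | 11.4.3 |
|---|---|---|
| Stratification factors | 3: site, age group, daily dose (6.2.1, 11.4.2) | 2: centre, age group |
| Symptom outcome | 1 score of 7 items (5.2) | 6 single items |
| Dizziness | included (5.2) | absent |
| Day-1 covariates | VAS, symptoms and blood pressure collected on day 1 (5.2) | none named |

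**3. Size of the dose omission.** Let R² be the share of outcome variance that dose explains. The protocol gives no value, so 5%, 10% and 20% are assumed. With dose fully balanced, the true variance of the treatment difference is (1 − R²) × 4σ²/N, while a model without dose reports 4σ²/N. The interval is therefore too wide by the factor 1/√(1 − R²). The actual level of a nominal two-sided 5% test is 2 × [1 − Φ(1.960/√(1 − R²))].

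| R² (assumed) | Interval too wide by | Actual level |
|---|---|---|
| 5% | 2.6% | 4.4% |
| 10% | 5.4% | 3.9% |
| 20% | 11.8% | 2.8% |

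The algorithm allocates with 70% probability to the arm that reduces the imbalance. Balance is therefore close but not perfect, and these are upper values for each R².

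**4. Which models are affected.** The corticotropin-test interaction model in 11.4.3 extends the primary Cox model, which is already stratified by dose. The models for the individual components are described as following the primary analysis, so they probably keep dose too. The linear models have no such link and take their covariates only from the two-factor list. That list is said to apply to every analysis, which leaves the Cox models unclear.

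**5. What day-1 adjustment would add.** With correlation r between the day-1 and follow-up values (assumed), residual variance is multiplied by 1 − r². This gives 0.91, 0.75 and 0.51 at r = 0.3, 0.5 and 0.7. The detectable difference at 80% power and two-sided 5% is (1.960 + 0.842) × √(4/N) × √(1 − r²).

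| N | unadjusted | r = 0.3 | r = 0.5 | r = 0.7 |
|---|---|---|---|---|
| 573 | 0.234 SD | 0.223 | 0.203 | 0.167 |
| 180 | 0.418 SD | 0.398 | 0.362 | 0.298 |

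The row for 180 applies only to follow-up blood pressure, because the VAS and symptoms are assessed in all participants. At r = 0.5 those 180 patients give the precision of 180/0.75 = 240. Cumulative doses and length of stay have no day-1 value.

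**6. Posture.** Sections 9.2.4.3, 9.3.2, 9.3.3 and 9.3.5 name two words for lying down. Sections 5.2 and 9.2.2 call for a standing reading, and 9.2.1, 9.2.2 and 9.2.4 describe an upright one at the clinical visits. For day 1 in particular, 5.2 asks for a standing pressure and 9.3.2 does not.

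**The case against.** The strongest reply is that the rule in 11.4.3 is sound and only its parenthesis is incomplete. Sections 6.2.1 and 11.4.2 say what the stratification variables are, so a careful analyst would include dose. On this view it is a slip of wording that errs on the conservative side and touches secondary outcomes only. That largely stands. The sentence still has to be corrected, because its general rule and its list give different models.

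A reader might go further and infer four things that the protocol does not support:

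- **That every secondary model drops dose.** The interaction model inherits it, and the component models probably do.
- **That baseline adjustment has been ruled out.** Section 11.4.3 is silent on it, and 11.4 leaves detailed methodology to an analysis plan that is not at hand. Adding day-1 values is an improvement, not the correction of an error.
- **That dose is a leading predictor of later symptoms or glucocorticoid use.** Dose is the first listed subgroup in 11.4.3, but no figure for its prognostic strength is given.
- **That no standing pressure is planned.** Sections 5.2, 9.2.1, 9.2.2 and 9.2.4 show the intent, so the wording in 9.2.4.3 and 9.3 looks like a drafting slip.

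On symptoms, the construction of the score can be left to the analysis plan, and 11.4.3 already allows generalised linear models if assumptions fail. Neither point explains why the declared score and dizziness are missing from the stated analysis.

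**Conclusion.** Two contradictions within the protocol stand. The covariate list in 11.4.3 disagrees with 6.2.1 and 11.4.2 on daily prednisone dose, and the symptom analysis in 11.4.3 disagrees with outcome 6 in 5.2. The first makes intervals from the linear secondary models too wide by roughly 3% to 12%. This rests on dose explaining 5% to 20% of outcome variance and on near-complete balance, both of which are assumptions. The effect is lost precision and conservative inference, not bias. The second leaves a declared secondary outcome without a stated analysis. The posture wording is a separate inconsistency that could cost data if sites follow 9.3 to the letter. The primary analysis, the non-inferiority conclusion and N = 573 are not touched. The point should be corrected, but it does not threaten the trial.

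**What to change.** - **11.4.3, covariates:** list centre, age group and daily prednisone dose at inclusion, and state that the Cox models for the interaction and the components keep the stratification of the primary model.
- **11.4.3, symptoms:** analyse the seven-item score including dizziness as declared in 5.2, with the single items as supportive.
- **11.4.3, precision (optional):** add the day-1 value as a covariate for the VAS, the symptom score and blood pressure.
- **9.2.4.3, 9.3.2, 9.3.3 and 9.3.5:** reconcile the positions with 5.2, 9.2.1, 9.2.2 and 9.2.4, so that the standing reading needed for the planned analysis is recorded.

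The analysis changes are wording only. They use data already scheduled and cost few degrees of freedom. The posture change also means informing the sites, and standing readings already missed cannot be recovered.
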